**4. PATIENT AND CENTRE SELECTION**

4.1 Number of patients

According to the case number calculation (Chapter 9.1), 212 patients, i.e. 106 patients per intervention group, are needed to achieve a power of 80% under the assumptions made. Since this is a non-randomised study, in which only one intervention is offered within a centre, recruitment should not be terminated until at least 106 patients have been enrolled in both arms. If the centres belonging to the same intervention arm have together reached the recruitment target of 106 patients, but the centres of the other arm have not yet reached it, recruitment may continue.

The recruitment and treatment of patients will be carried out in the respective study centres. Each centre participating in the study should be able to enrol at least 10 patients within the planned recruitment period of 24 months.

If the total number of cases is not reached by the planned recruitment end (31.01.2020), the recruitment period may be extended if necessary. If recruitment is accelerated, recruitment will be terminated earlier accordingly.

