9.1 Case Number Calculation

The calculation of the number of cases refers to the primary endpoint, the technical success rate. In the literature, rates of approximately 95% are given in similar studies (Lee et al. (2016)). This is assumed for both groups. If the technical success rate in the PTBD group is less than 10% lower than in the EUCD group, it is considered clinically irrelevant based on clinical judgment. Therefore, the non-inferiority threshold is defined as δ=0.1. At a unilateral significance level of 2.5%, 200 patients (100 per group) are required to perform a Farrington/Manning test at 80% power (calculations with PASS 14.0.8). It is assumed that for a very small proportion of patients the primary endpoint will not be met (for example, if a complication leads to premature discontinuation of the intervention). Therefore, at least 106 patients per group should be included to compensate for a loss of information due to 5% assumed drop-outs.

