9.2 Statistical evaluation

The primary endpoint is the technical success rate in malignant distal choledochial stenosis using a self-expanding metal stent. The non-inferiority of PTBD compared to EUCD shall be demonstrated. The corresponding test hypothesis is

H0: pEUCD - pPTBD ≥ δ vs. H1: pEUCD - pPTBD < δ

Where pPTBD describes the technical success rate in the EUCD group, pPTBD the technical success rate in the PTBD group and δ=0.1 the non-inferiority limit.

The non-inferiority of PTBD to EUCD is verified by the Farrington/Manning test with a one-sided significance level of 2.5%.

Since this is a non-inferiority study, the primary evaluation will be based on both the Intention-To-Treat (ITT) Set and the Per-Protocol (PP) Set. In the ITT set, all patients are considered in whom the intervention was performed, even if it was technically unsuccessful or participation in the study was terminated prematurely. If the intervention has to be terminated prematurely (e.g. due to organ perforation), this patient is included in the primary evaluation. The primary evaluation is based on the assumption of technical failure in these patients.

In the PP Set, only those patients are included in the evaluation for whom the intervention was performed and the technical success was measured.

In sensitivity analyses, best case and worst case scenarios are calculated for the missing values. In addition, regression models are planned to investigate the influence of confounders on the endpoints. The variables intervention (EUCD with subgroups or PTBD with side localisation), BMI or bilirubin value are considered as input variables in the baseline study. The binary outcome variable is the technical success of the intervention. The affiliation of the individual patients to the two evaluation collectives is defined in SAP before the database is closed.

If non-inferiority can be shown with regard to the technical success rate, the occurrence of at least one complication (expected complication rate for both interventions: 10-20%) is compared hierarchically in the next step and tested for differences between the groups (based on the ITT set). Due to the hierarchical approach, the full level alpha, in this case two-sided 5%, is tested.

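### The Per-Protocol set is defined by whether technical success was measured, not by adherence, and so most naturally drops aborted procedures that ITT counts as failures

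*Protocol*

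**What the plan says.** Protocol section 9.2 names ITT and PP as joint bases of the primary evaluation, giving the non-inferiority design as the reason.

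- **ITT:** "In the ITT set, all patients are considered in whom the intervention was performed, even if it was technically unsuccessful".
- **PP:** "In the PP Set, only those patients are included in the evaluation for whom the intervention was performed and the technical success was measured".
- **Procedures stopped early** (organ perforation is the example) belong to the primary evaluation: "The primary evaluation is based on the assumption of technical failure in these patients".

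Both sets require that the intervention was performed. The only further condition for PP is that the outcome was measured; no adherence criterion appears. The section leaves the assignment of individual patients to the SAP and does not state how the two results combine into a claim.

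Two other sections bear on the reading. Section 9.1 adds 5% per group for lost information and illustrates it with an intervention discontinued after a complication. Section 6.3 records technical success as yes or no on the day of the intervention.

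**The concern.** A PP analysis in a non-inferiority trial is meant to remove protocol deviations that could blur a real difference between the arms. Here membership turns on whether the endpoint was obtained. An outcome that has to be assumed is most naturally one that was not measured, and section 9.1 treats an aborted procedure as lost information. On that reading, patients whom ITT counts as failures leave PP altogether.

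Aborted procedures are among the clearest failures of this endpoint. Removing them raises the success rate in any arm that has them. If PTBD has more of them, or if aborts are a fixed share of failures and PTBD is truly worse, the PP difference shrinks towards zero. The second case is the one that a non-inferiority test has to guard against. The confirmatory complication comparison in section 9.2 opens only after non-inferiority is shown, so it depends on the same rule.

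**Working it through.** **Inputs from the protocol.** Section 9.1 takes a success rate of about 95% in each arm and an absolute margin of 0.10, and gives the resulting size: "At a unilateral significance level of 2.5%, 200 patients (100 per group) are required to perform a Farrington/Manning test at 80% power". Section 4.1 carries the total after the drop-out allowance, 212 patients or 106 per group. The protocol gives no abort rate for either arm, so every abort rate below is an assumption.

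**1. The plan's own sample size.** Farrington/Manning, true rates 0.95 and 0.95, margin 0.10. The rates restricted to the null boundary are 0.8703 (PTBD) and 0.9703 (EUCD).

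- s0 = √(0.8703·0.1297 + 0.9703·0.0297) = √(0.1129 + 0.0288) = 0.3764
- s1 = √(2·0.95·0.05) = 0.3082
- n = [(1.960·0.3764 + 0.8416·0.3082)/0.10]² = 99.4, so 100 per group
- With 5% loss: 100/0.95 = 105.3, so 106 per group

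Both stated figures reproduce.

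**2. What deletion does to the true PP rates.** With success rate p and abort rate a, ITT estimates p and PP estimates p/(1 − a). At the margin with half of each arm's failures aborted:

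- PTBD: 0.85/(1 − 0.075) = 91.9%
- EUCD: 0.95/(1 − 0.025) = 97.4%

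The PP difference is 5.5 points where the true difference is 10.

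**3. Type I error at the margin.** Rates 85% and 95%, 106 per arm, one-sided 2.5%, 40,000 simulated trials per row. ITT counts aborts as failures and PP deletes them.

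| Assumed aborts PTBD / EUCD | PP difference (points) | PP alone | Both must reject |
|---|---|---|---|
| 7.5% / 2.5% (half of failures) | 5.5 | 21.4% | 2.2% |
| 5% / 0% | 5.5 | 18.8% | 2.4% |
| 10% / 2.5% | 3.0 | 53.7% | 2.4% |
| 15% / 5% (all failures) | 0.0 | 100% | 2.4% |
| 2.5% / 2.5% | 10.3 | 1.8% | 1.1% |
| 5% / 5% | 10.5 | 1.4% | 0.6% |
| 1% / 4% | 13.1 | 0.2% | 0.2% |
| 0% / 5% | 15.0 | 0.02% | 0.02% |

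If PP keeps aborts as failures, its error equals that of ITT: 2.35% by exact calculation.

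**4. Single-trial examples.** z = (p̂PTBD − p̂EUCD + 0.10)/SE, with SE from the restricted rates.

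- *Aborts in both arms* (8 PTBD, 3 EUCD). ITT, 93/106 against 101/106: z = (−0.0755 + 0.10)/0.0389 = 0.63, p = 0.26. PP, 93/98 against 101/103: z = (−0.0316 + 0.10)/0.0337 = 2.03, p = 0.021. ITT does not show non-inferiority; PP does.
- *Five PTBD aborts, none in EUCD.* ITT, 96/106 against 101/106: p = 0.081. PP, 96/101 against 101/106: p = 0.0042. The result reverses.
- *Same trial, but four of the five EUCD failures are also aborts.* PP, 96/101 against 101/102: p = 0.028, no reversal. If all five are aborts, 96/101 against 101/101: p = 0.045, again none.

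**5. At the design rates** (95% and 95%) with 2.5% aborts in each arm, PP power rises from about 85% to 96%, although nothing about the treatments has changed.

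**The case against.** A reader might infer that PP certainly drops every aborted procedure. The protocol does not say so. The failure rule is written for the primary evaluation, which section 9.2 bases on both sets, so it can be read as covering PP. The yes/no field in section 6.3 also allows a procedure stopped without a stent to be a measured no. This objection stands: deletion is the more natural reading, not a stated rule. The other reading does not rescue PP, however. If aborts are measured failures, the definition excludes almost nobody and PP nearly duplicates ITT.

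A reader might also infer that PP always favours non-inferiority. The table shows otherwise: equal or EUCD-heavy aborts make PP stricter, and the reversal with five PTBD aborts disappears once EUCD has four or five. The 5% in section 9.1 is an allowance for each group, not an abort rate for PTBD.

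Third, a reader might infer that the trial's overall error is inflated. If both sets must reject, it is not: ITT caps the joint error at about 2.4%. Inflation would reach the claim only if PP alone could carry it, which the protocol neither says nor rules out.

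Finally, set membership is deferred to the SAP. That answers any complaint that the protocol lists no deviations, since such detail commonly sits there. It does not answer the membership criterion itself, which section 9.2 already fixes.

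**Conclusion.** The concern holds in a conditional form. Section 9.2 fixes a PP criterion that depends on outcome availability. With section 9.1, it most naturally removes from PP patients whom ITT counts as failures.

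On that reading, the bias is towards non-inferiority when aborts are more frequent in PTBD or track failures: about 21% type I error for PP alone in the half-of-failures case, against about 2.4%. It runs the other way when aborts are equal or EUCD-heavy. These sizes rest on assumed abort rates.

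Under a both-must-reject rule the damage is limited to a PP analysis that gives no valid second check. The protocol stops short of stating that rule. This is a point that should be fixed; it does not by itself invalidate the primary analysis.

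**What to change.** In section 9.2, and in step with it in the SAP:

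1. State that any started procedure that is aborted or unsuccessful is a technical failure in both ITT and PP.
2. Define PP as the ITT set minus patients with major protocol deviations, on a list fixed before database lock, and drop the condition that technical success was measured.
3. State that non-inferiority is claimed only if both sets reject at the one-sided 2.5% level.
4. Align the drop-out example in section 9.1, so that an aborted procedure is no longer described as lost information.

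The cost is wording, with no new data and no change to the 106 per group. PP success rates will be slightly lower than under the present definition.

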**5. TREATMENTS/ INTERVENTIONS**

5.1 Description of the treatment(s)/ intervention(s)

PTBD

PTBD is performed in the first step by means of (colour contrast Doppler) ultrasound-guided puncture of an (dilated) intrahepatic bile duct using an access needle (e.g. Chiba needle (22G/0.7mm diameter). In the next step, the application of contrast medium into the bile duct system is performed under radiological fluoroscopy. The access route should be at a sufficient safety distance from neighbouring structures, i.e. the pleura in case of right-sided access.

Ideally, after KM filling of the bile duct system, a wire should be advanced distally beyond the stenosis in the common bile duct. This can also be done after changing to a larger wire (from 0.018" to 0.035"). After placement of an appropriate guide wire, a corresponding metal stenosis implantation (SEMS) should be performed in the same session in the area of the stenosis of the common bile duct (usually 8 or 10 mm diameter with different lengths (usually 6 -10 cm).

For further precision, the release of the metal stent can (not obligatory) be controlled by an additional luminal endoscopic visualization. (usually in relation to the papilla or the protrusion into the duodenum). This is particularly relevant with regard to endoscopic reintervention. Even in cases of tumour-related duodenal stenosis (use of a thinner endoscope) or altered anatomy after abdominal surgery (e.g. access via the feeding loop after Billroth II surgery). it is very often possible to reach the papilla (e.g. using a gastroscope).

Leaving a percutaneous plastic drainage after successful implantation of a metal stent should be avoided (counted as reintervention). If metal stent implantation is not possible in the initial PTBD, an internal/external plastic drainage should be inserted and the sole external drainage should be avoided (highest risk of complications).

EUCD

Endosonographically controlled cholangiodrainage (EUCD) is performed according to the current state of knowledge of this technique (2-9,14,15).

The choice of the respective EUCD method depends on the examiner. First and foremost, however, an antegrade stenting in the sense of an EUS-AD (wire is passed over the stenosis) should be performed.

should be attempted, since - in contrast to the transluminal procedure - the original anatomy of the bile duct system is preserved and the least complications are expected.

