In the event of unsuccessful wire advancement via the tumor stenosis in the context of an intended EUS-AD, the next step should be an EUS-guided transhepatic drainage (EUS-HD) with metal stent implantation or EUS-guided choledochal drainage (EUS-CD) with metal stent implantation. The respective access route - transesophageal, transgastral, transduodenal or transenteral - depends on the disease or anatomy (e.g. in the case of Roux Y anastomosis transenteral). In the evaluation of this study, the respective, access-path dependent interventions are subsumed under the designations of an EUS-HD or an EUS-CD.

EUS-guided interventions such as the EUS-guided rendezvous procedure, EUS-guided cholecystomy or EUS-guided jejunostomy, which is used e.g. in afferent loop syndrome and usually requires the use of a lumen apposing metal stent (LAMS), are not the subject of this study.

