The evaluation of further secondary endpoints is done in the ITT set. With regard to the complication rate, PTCD is expected to have a lower complication rate than EUCD. No missing values are implanted during the evaluation of secondary endpoints. The evaluation is purely descriptive. Appropriate statistical methods are used according to the underlying distribution. For continuous endpoints, the mean, standard deviation, median, interquartile distance, and minimum and maximum are reported separately and in total for the two groups. For categorical endpoints, absolute and relative frequencies are given, also separately for the two groups and in total. Event times are displayed and evaluated using survival time analysis methods (e.g. Kaplan Meier). Descriptive p-values are given together with 95% confidence intervals. In the EUCD group, descriptive p-values are also divided by method (see 5.1). In addition, unless defined in the secondary endpoints, adverse events are evaluated and compared.

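### EUCD results are split by technique without saying whether the label is the first-attempted or the final technique; labelled by final technique, the comparison tends to favour EUS-AD

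*Protocol*

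**What the plan says.** Protocol section 5.1 describes an order of attempts within EUCD. On antegrade stenting it says: "First and foremost, however, an antegrade stenting in the sense of an EUS-AD (wire is passed over the stenosis) should be performed". On what follows: "In the event of unsuccessful wire advancement via the tumor stenosis in the context of an intended EUS-AD, the next step should be" EUS-HD or EUS-CD with a metal stent. The same section also says: "The choice of the respective EUCD method depends on the examiner". Some EUS-HD and EUS-CD procedures may therefore be direct choices.

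Section 9.2, in the paragraph on further secondary endpoints, says: "In the EUCD group, descriptive p-values are also divided by method (see 5.1". Earlier, 9.2 plans a regression with technical success as the binary outcome, in which the intervention variable enters with the EUCD subgroups.

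Three other places bear on the point.

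- Section 2 ties the secondary endpoints and their time points to the technically successful intervention, and times EUCD from insertion to removal of the endoscope.
- Section 6.3 lists EUS-AD, EUS-HD and EUS-CD as data items. For PTBD it lists a count of procedures before the metal stent. It has no corresponding item for EUCD, such as the technique tried first or a change of technique.
- Section 9.2 counts interventions that had to be stopped early as technical failures.

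**The concern.** Under the sequence in 5.1, a patient's technique can be settled during the procedure by how the first attempt goes. A label of that kind is a post-baseline variable, partly produced by the course being compared. The protocol does not say whether the label is the first-attempted or the final technique. Final technique is the natural reading, because endpoints refer to the technically successful intervention.

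On that reading, patients whose wire did not pass in an EUS-AD attempt are counted under EUS-HD/CD. Those groups then carry the time of the failed attempt, and possibly harder anatomy and the complications of two attempts. Section 5.1 already expects the fewest complications with EUS-AD, so a comparison distorted in that direction could be taken as confirmation. The regression has the same weakness, since the regressor is partly a consequence of how the procedure went. A later SAP can define the groups, but it cannot recover an order of attempts that was never recorded.

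**Working it through.** **The plan's own figure.** Inputs from section 9.1: "rates of approximately 95% are given in similar studies", taken for both arms; "the non-inferiority threshold is defined as δ=0.1"; one-sided 2.5%, 80% power. The restricted estimates under the null are 0.9703 and 0.8703.

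- s0 = √(0.9703×0.0297 + 0.8703×0.1297) = 0.376
- s1 = √(2×0.95×0.05) = 0.308
- n = ((1.960×0.376 + 0.842×0.308)/0.1)² ≈ 99.4, so 100 per group
- 100/0.95 = 105.3, so 106 per group

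The stated sample size is reproduced and is not at issue. It supplies N = 106 for the EUCD arm below.

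**Assumptions.** The protocol gives no wire-passage rate, no share starting with EUS-AD and no procedure times. All of these are assumed and varied:

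- f, share starting with EUS-AD: 100%, 70%, 50%
- w, wire passage among those: 40%, 60%, 80%
- duration: mean 45 min, SD 20, the same for every technique
- time lost on a failed EUS-AD attempt in the same session: 10 or 20 min

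**Duration, labelled by final technique.** The share of the EUS-HD/CD group that consists of failed EUS-AD attempts is f(1−w)/(1−fw). Multiplied by the time lost, it gives the expected difference between equal techniques. With w = 60% and 20 min lost:

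- f = 100%: 0.40/0.40 = 1.00, difference 20 min
- f = 70%: 0.28/0.58 = 0.48, difference 9.7 min
- f = 50%: 0.20/0.70 = 0.29, difference 5.7 min

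Share of 2000 simulated arms of 106 patients in which a t-test of EUS-AD against EUS-HD/CD gives p<0.05 (about 5% expected without the artefact):

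| f | w | 10 min lost | 20 min lost |
| --- | --- | --- | --- |
| 100% | 40% | 71% | 100% |
| 100% | 60% | 70% | 100% |
| 100% | 80% | 53% | 98% |
| 70% | 40% | 26% | 69% |
| 70% | 60% | 22% | 62% |
| 70% | 80% | 14% | 36% |
| 50% | 40% | 11% | 28% |
| 50% | 60% | 10% | 22% |
| 50% | 80% | 7% | 11% |

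Monte Carlo standard error is at most √(0.25/2000) = 1.1 percentage points.

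**Technical success, all starting with EUS-AD.** Two cases must be kept apart.

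1. Stenting succeeds in 95% whichever technique is finally used. Both labels then show 95% and there is no gap. What the label hides is that an antegrade stent is achieved in only 0.95×w of attempts: 38%, 57% and 76% for w = 40%, 60% and 80%.
2. Failed passage also marks harder cases. Set success to 98% where the wire passes and hold the arm at 95%. Success under EUS-HD/CD is then (0.95 − 0.98w)/(1 − w): 90.5% for w = 60%, 88% for 70%, 83% for 80%. Fisher's test gives p<0.05 in 32%, 49% and 64% of simulated arms.

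**The case against.** The strongest reply is that the protocol never says patients are grouped by final technique. The label is simply undefined, and a descriptive subgroup is ordinarily defined in the SAP, which is not shown. This stands, so the finding is conditional on the label. It does not dispose of the point, because the order of attempts is not among the items in 6.3. Those items carry no single-choice restriction such as 6.2 uses elsewhere. If several techniques can be ticked, a switch might be inferred from the combination, so it cannot be said that switches are certainly lost. The protocol just does not require them to be recorded.

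A reader might also infer that EUS-AD looks better by construction and keeps only its successes. The documents do not support that. The examiner may go directly to EUS-HD or EUS-CD, which dilutes the effect, as the rows for f = 50% show. A procedure stopped during EUS-AD counts as a technical failure and may well stay under EUS-AD, which pulls technical success the other way.

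The sentence in 9.2 could also mean each technique against PTBD rather than technique against technique. The selection enters either comparison.

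Finally, these p-values are descriptive, and section 2 sets no objective of ranking EUCD techniques. That is right, and it limits the severity.

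**Conclusion.** The point holds in conditional form and is minor. Sections 5.1 and 9.2 together allow a comparison in which the group label partly reflects whether the first attempt worked, and the protocol neither defines the label nor lists the item needed to avoid this. If the label is final technique, EUS-AD tends to be favoured. Duration is the clearest case: under the stated assumptions p<0.05 arises between equal techniques in about 53-100% of trials if all start with EUS-AD, 14-69% if 70% do, and 7-28% if half do. For technical success, grouping by final technique creates no gap by itself; one appears only if failed wire passage also marks harder cases. No effect on complications was quantified.

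It would be a mistake to read this as a threat to the main results. The non-inferiority test and the hierarchical complication test compare whole arms and do not use the technique label.

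**What to change.** Add a CRF item for the first-attempted EUCD technique and for any switch, and list it in section 6.3. In section 9.2, state that EUCD results are reported by first-attempted technique, with the number switching. Also state whether the p-values compare the techniques with each other or each with PTBD. Present results by final technique descriptively, without p-values. In the regression for technical success, replace final technique by first-attempted technique or by the EUCD/PTBD arm alone.

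Dropping the p-values for final technique is partly a matter of reporting style, but it avoids attaching a test to a difference that the order of attempts can produce. The cost is one CRF field and slightly more analysis work. Patient management and sample size do not change.
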